# The effect of a six-week osteopathic visceral manipulation in patients with non-specific chronic low back pain and functional constipation: study protocol for a randomized controlled trial

**DOI:** 10.1186/s13063-018-2532-8

**Published:** 2018-03-02

**Keywords:** Visceral manipulation, Low back pain, Constipation, Flexion-relaxation, Electromyography

## Abstract

**Background:**

The aim of the proposed study is to analyze the effect of a six-week osteopathic visceral manipulation (OVM) program on the flexion-relaxation phenomenon in individuals with non-specific chronic low back pain (LBP) and functional constipation.

**Methods/Design:**

An assessor-blinded, two-arm, randomized, placebo-controlled trial will be conducted. The sample will comprise 76 individuals with non-specific chronic LBP who have functional intestinal constipation, aged 18–65 years. The participants will be randomly allocated to two groups: (1) OVM and (2) sham OVM (SOVM). Evaluations will involve an interview, the Oswestry Disability Index, Fear-Avoidance Beliefs Questionnaire, functional constipation according to Rome III criteria, Biering-Sorensen test to normalize electromyographic (EMG) data, T12–L1 paraspinal level of the EMG signal during the flexion-relaxation phenomenon, 11-point numeric pain rating scale and fingertip-to-floor test. OVM and SOVM will be performed once per week for six weeks. Group 1 will receive OVM for 15 min and Group 2 will receive a sham visceral technique. Evaluations will be performed before and after the first session, after six weeks of treatment, and three months after randomization (follow-up). The findings will be analyzed statistically considering a 5% significance level (*p* ≤ 0.05). The limitation of the study is that the therapist will not be blinded.

**Discussion:**

This will be the first trial to analyze the clinical response and electromyographic signals during the flexion-relaxation phenomenon after OVM.

**Trial registration:**

Brazilian Clinical Trial Registry, RBR-7sx8j3. Registered on 26 October 2017.

**Electronic supplementary material:**

The online version of this article (10.1186/s13063-018-2532-8) contains supplementary material, which is available to authorized users.

## Background

Recent research shows that low back pain (LBP) can cause more years of disability than any other health condition [1]. Chronic pain is a public health problem, as it is an important cause of morbidity, work absenteeism, and temporary or persistent incapacity, generating high costs for healthcare systems [2]. There is an increasing demand for the treatment of chronic LBP [3] and researchers report that 80–90% [4–6] of cases are classified as non-specific LBP.

LBP is considered the second most common reason for visits to first-contact practitioners, such as chiropractors and osteopaths [7]. Besides using spinal manipulation [8–10], these professionals also employ visceral techniques [11] with a conservative approach. The theory is that visceral disorders could potentially trigger or exacerbate LBP symptoms due to impaired movement between internal organs and respective supporting tissues. This could manifest as LBP through two possible mechanisms: referred visceral pain and central sensitization [11].

Studies have shown that visceral techniques applied to healthy individuals lead to an immediate increase in the pain threshold of the low back compared to placebo application [12]. Researchers have also studied specific visceral disorders, such as refractory irritable bowel syndrome [13] and chronic constipation in women [14], and found better results after visceral treatment. While some researchers have performed visceral techniques on patients with LBP [11, 15, 16], the physiological and biomechanical mechanisms remain untested.

There is evidence that patients with LBP have deficits in the neuromuscular control of the spine [17–19] and that electrical activity of the trunk muscles can be used to evaluate the effects of therapeutic interventions [19–21] as well as differentiate individuals with LBP, as such individuals have higher electromyographic signals compared to asymptomatic individuals [17, 18, 22–24]. However, it is not known whether the abnormal electromyographic (EMG) activity in the paraspinal muscles of patients with LBP is the cause or consequence of pain [24, 25].

Individuals with chronic LBP do not reach the flexion-relaxation phenomenon (FRP), which is the decrease in or absence of electromyographic activity in the paraspinal muscles found during full trunk flexion in asymptomatic individuals [17–19]. In patients with LBP, the absence of this phenomenon may be due to muscle spasms, decreased range of motion, exaggerated stretch reflexes, or the protection of injured passive structures [26].

Based on the literature, there are indications that the FRP may be a valuable clinical tool to assist in the diagnosis and treatment of patients with LBP [17, 18, 24, 27] and there have been very few studies on the use of visceral techniques for such patients. Thus, the aim of the proposed study is to determine whether osteopathic visceral manipulation (OVM) can modulate stabilizing neuromuscular responses of the lumbar spine and reduce both pain intensity and disability in individuals with non-specific chronic LBP and functional intestinal constipation.

### Primary objective

The primary objective of the proposed study is to analyze the effect of a six-week OVM program on pain intensity and the disability index in individuals with non-specific chronic LBP and functional intestinal constipation.

### Secondary objective

The secondary objective of the proposed study is to analyze the effect of a six-week OVM program on EMG signals of paraspinal muscles during the FRP, the global flexibility, and the fear-avoidance beliefs in individuals with non-specific chronic LBP and functional intestinal constipation.

### Hypothesis

The authors hypothesize that the group submitted to OVM will experience more beneficial effects compared with similar individuals who receive placebo visceral techniques.

### Study design

An assessor-blinder, two-arm, placebo-controlled RCT will be conducted.

## Methods/Design

### Sample selection

Individuals with non-specific chronic LBP will be recruited from physical therapy clinics in the city of Rondonópolis, state of Mato Grosso, Brazil and will be selected based on the eligibility criteria listed below.

### Inclusion criteria

Age 18–65 years [28]Non-specific LBP for at least three months [28]Pain intensity of at least 2 points measured using the Numeric Pain Rating Scale [11]Functional constipation according to Rome III criteria [29]

### Exclusion criteria

Any contraindication to OVM or having undergone treatment in the previous six monthsHaving undergone spinal surgery in the previous six monthsSerious spinal pathology (e.g. metastasis, spinal fracture, inflammatory, and infective diseases, caudal equine syndrome, canal stenosis)Serious cardiovascular or metabolic diseasePregnancyRed flag signals [5]Currently in an acute inflammatory phase of known gastrointestinal or urinary diseases (such as cholecysticis, renal calculi, peritonitis, appendicitis)

### Intervention

The participants will be allocated to groups receiving one of two interventions: (1) OVM or (2) sham OVM (SOVM). The participants in each group will receive six sessions (one per week for six weeks) (Table 1). Given the nature of the study, it is not possible to blind the therapist, but the assessor and patients will be blinded to the treatment conditions. For ethical reasons, the patients in both groups will receive an information booklet called The Back Book in Portuguese [30] on the first day of treatment.

### Group 1: osteopathic visceral manipulation

This group will receive OVM (15 min per session, one session per week for six weeks). The OVM techniques that will be used are described by Ricard [31] and will be performed by a single osteopath with more than ten years of experience. In the first part of each consultation, all patients will be submitted to a direct visceral evaluation [12]. Each treatment will be individualized for each patient using specific visceral manipulation techniques [11, 16] involving light or deep manual fascial releases as well as specific small and large intestine mobilizations in the abdomen, as appropriate [31].

### Group 2: sham technique

This group will receive SOVM at the same time as Group 1 (15 min per session, one session per week for six weeks), which will involve just light touches over the different parts of the abdomen, without any deep mobilization or movement. The osteopath will apply her hands over the same points with the same duration as in OVM to give the patient the perception of being treated [11–13, 15].

### Outcome measures

A blinded assessor will record outcome measures.

The primary outcomes will be LBP intensity (NPRS) and the Oswestry Disability Index (ODI) after the six weeks of treatment and three months after randomization, because pain is the most common reason patients seek private physical therapy clinics for the treatment of LBP. From a patient’s perspective, it is also the outcome that most determines whether treatment has been successful [32].

The secondary outcomes will be the EMG signals during the FRP and fingertip-to-floor test (FFT) after the first treatment session, after the six weeks of treatment and three months after randomization and the FABQ after the six weeks of treatment and three months after randomization.

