### Sample size calculation

The sample size was calculated using G Power 3.1.9.2 software. This calculation was based on the detection of a 10-point difference on the ODI and 2.5-point difference on the NPRS, which have been identified as the minimum clinically important differences [33]. A sample size of 32 participants per group would provide a 90% power to detect a clinically important difference between groups, assuming a common standard deviation of 12 on the ODI [34] and 3.0 on the NPRS and a two-sided hypothesis with an alpha level of 0.5. The sample will be increased by 20% to compensate for possible dropouts, leading to 38 individuals in each group (overall sample = 76 participants).

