### Statistical analysis

Statistical analysis will be performed using intention-to-treat analysis. If data losses occur during the study, the last observation will be carried forward to adjust the missing data in follow-up evaluations. The Shapiro–Wilk test will be used to determine the normality of the data. Anthropometric differences between groups will be determined using the independent t-test for data will normal distribution and the Mann–Whiney test for data with non-normal distribution. Repeated-measures analysis of variance (ANOVA) followed by the Bonferroni post hoc test will be used to determine the effects of treatment with regard to the NPRS, RMDQ, FFT, FABQ, and EMG considering the following interactions: group (OVM and SOVM) vs evaluation (pre-interventions, after one session, after six weeks, and three months after randomization) vs movement (flexion extension). If the data exhibit non-normal distribution, Friedman’s ANOVA will be used with Dunn’s post hoc test. A *p* value < 0.05 will be considered indicative of statistical significance. The data will be organized and tabulated using the Statistical Package for the Social Sciences (SPSS, v.19.0).

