## Discussion

This paper presents a detailed description of a prospective, placebo-controlled, assessor-blinded, clinical RCT designed to demonstrate the effect of a six-week OVM program on the FRP in individuals with non-specific chronic LBP and functional constipation. It will also allow us to investigate neurophysiologic and biomechanical processes that may contribute to the therapeutic effects of OVM. Analyzing FRP measured in patients with LBP submitted to OVM may help clarify the contributions of passive and active structures during and following OVM, thereby providing evidence for suspected therapeutic mechanisms. The results will be published and the evidence found may contribute to the use of visceral manipulation for this population.

The results and practical relevance of our study will be of importance not only for researchers and policy makers but also for patients suffering from non-specific chronic LBP and functional intestinal constipation.

Given the nature of the study, the limitation of the study is that the therapist will not be blinded. Nevertheless, the design also has important strengths: reproducibility; and the blinding of the assessor and participant. The outcome will provide evidence-based conclusions regarding the effectiveness of this treatment for the management of patients with non-specific chronic LBP and functional constipation.

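### Two co-primary outcomes at two time points have no success rule and no adjustment across outcomes (about 7–10% error if either may win), and the abstract and discussion name a secondary outcome as the aim

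*Protocol article*

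**What the plan says.** - **Primary objective:** to "analyze the effect of a six-week OVM program on pain intensity and the disability index".
- **Outcome measures:** this section states "The primary outcomes will be LBP intensity (NPRS) and the Oswestry Disability Index (ODI) after the six weeks of treatment and three months after randomization". That makes two outcomes at two time points, or four outcome-by-time combinations. The same section lists the EMG signals during the FRP as secondary, as does the Secondary objective.
- **Statistical analysis:** one repeated-measures ANOVA approach over four evaluations, followed by a Bonferroni post hoc test, with Friedman and Dunn as the non-normal alternative. A p "value < 0.05 will be considered indicative of statistical significance". The comparisons that make up the Bonferroni family are not defined, and nothing is said about adjustment across outcomes. The list of analysed variables contains the RMDQ and not the ODI.
- **Sample size calculation:** "A sample size of 32 participants per group would provide a 90% power to detect a clinically important difference between groups", with a 10-point ODI difference (SD 12) and a 2.5-point NPRS difference (SD 3.0).
- **Abstract, Background:** the aim is given as the effect of an "osteopathic visceral manipulation (OVM) program on the flexion-relaxation phenomenon in individuals with non-specific chronic low back pain".
- **Discussion:** the trial is "designed to demonstrate the effect of a six-week OVM program on the FRP".

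**The concern.** A confirmatory trial needs one declared route to a positive result. This text leaves several open: pain or disability, week 6 or month 3. Because the abstract and discussion present the FRP as what the trial sets out to show, a positive EMG result could also be presented as the main finding. If the successful result can be picked afterwards, the error rate for the primary claim is no longer the nominal 5%. The 90% power also cannot be matched to a success rule, because none is stated.

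**Working it through.** **1. Reproducing the sample size.** Standardised difference: 10/12 = 0.833 for the ODI and 2.5/3.0 = 0.833 for the NPRS. Normal approximation at two-sided 0.05 and 90% power: n = 2 × (1.960 + 1.282)² / 0.833² = 30.3, so 31 per group. The exact noncentral t calculation gives 32 per group with power 90.7%. The stated 32 is therefore reproduced for each outcome taken alone. It needs alpha 0.05; the printed alpha of 0.5 would need only 12 per group by the normal approximation.

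**2. Error rate under an either-outcome reading.** The document gives no correlation between outcomes or between visits, so these are assumptions.

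| How the plan is read | Chance of at least one false-positive primary result |
|---|---|
| One ANOVA interaction test per outcome at 0.05, either may win | 1 − 0.95² = 9.75% if independent; 8.5–9.7% simulated for between-outcome correlation 0–0.7 |
| Bonferroni over the two primary visits within each outcome (0.025 per contrast) | 1 − 0.975⁴ = 9.6% if independent; 8.2% at common correlation 0.5; 7.0% at 0.7 |
| Bonferroni at 0.0125 per contrast | at most 1 − 0.9875⁴ = 4.9% |
| Four visit contrasts, each read unadjusted at 0.05 | 1 − 0.95⁴ = 18.5% if independent; 14.4% at common correlation 0.6 |
| Both outcomes required, one test each at 0.05 | at most 5% |

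The first two rows are closest to the written plan, which has a test per outcome with Bonferroni inside it and nothing across outcomes. They give about 7–10%.

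**3. Power under each success rule** (32 per group, true difference 0.833 SD on both outcomes):
- One given outcome at 0.05: 90.7%.
- Both outcomes at 0.05, one time point: 0.907² = 82% if uncorrelated, rising to about 86% at correlation 0.7.
- One given outcome at 0.025: 84.7%.
- At least one of the two at 0.025: 1 − (1 − 0.847)² = 97.7% if uncorrelated, about 92% at correlation 0.7.

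**4. The stated aim.** The Primary objective and Outcome measures sections put pain and disability first. The Secondary objective and Outcome measures sections put the FRP second. The abstract and the Discussion reverse this. The contradiction is one of text and contributes nothing to the rates in step 2.

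**The case against.** **The success rule and cross-outcome multiplicity are often left to the SAP, which is not shown.** That is fair for the detail. But the article itself fixes two primary outcomes at two time points, one threshold, a power statement and two conflicting aims, and these do not fit together as written.

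**The wording leans towards both outcomes.** The last paragraph of the Background speaks of reducing both pain and disability, and the Primary objective joins the two. If both were required, with one test each, 5% would hold without adjustment. This stands as a possibility, but neither sentence is a success rule, and the stated 90% would then overstate the power at 32 per group. With all 38 enrolled per group completing, power to win on both would be about 90–92%.

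**Stronger readings to avoid.** A reader might infer four tests each at 0.05 and an error rate of 14–19%. The Statistical analysis section does not support this: it places a Bonferroni step after each ANOVA, and those figures need the visit contrasts to be read unadjusted. A reader might also take 84.7% as the power of an error-controlled either-outcome rule. It is the power for one named outcome at 0.025; the rule itself has about 92–98% if both effects are real, so the sample size is not too small for it.

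**Conclusion.** The point holds as a should-fix. Under an either-outcome reading, the written ANOVA-plus-Bonferroni plan gives about a 7–10% chance of at least one false-positive primary result. This assumes correlations from 0 to 0.7 and that the post hoc family covers the two primary visits, or that one interaction test decides each outcome. Because the family is undefined, the rate could fall just below 5% or reach 18.5%. The figures apply to the ANOVA route only; the Friedman alternative makes no between-group comparison. The 90% power is correct per outcome and falls to about 82–86% if both must succeed at 32 per group. The FRP wording is a separate inconsistency. The objectives and outcomes sections agree with each other on this, so it does not show that the FRP is meant to be primary.

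**What to change.** Before unblinding:
1. Declare the between-group NPRS contrast at week 6 as the lead primary test at two-sided 0.05. This follows the protocol's own rationale in Outcome measures, which justifies the primary outcomes through pain.
2. Test the remaining primary contrasts in a prespecified fixed sequence, for example ODI week 6, NPRS month 3, ODI month 3, stopping at the first non-significant result. This holds the error rate at 5% across all four.
3. State that the 90% power applies to the first test.
4. Replace the RMDQ with the ODI in the Statistical analysis section, so that the second primary outcome has a named analysis.
5. Correct the abstract and Discussion so that pain and disability are the primary aim and the FRP is secondary.

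Cost: no extra patients, and the lead test keeps 90.7% power at 32 per group. It is more than a wording change, because ordered between-group contrasts become the deciding analysis and the ANOVA moves to a supporting role. Later claims depend on every earlier test succeeding. The pain rationale supports NPRS first, but the order of the later steps is a choice for the investigators. If they intend both outcomes to be required, they should say so, name the leading time point and restate the power.

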### Participants’ timeline

A brief Standard Protocol Items: Recommendations for Interventional Trials (SPIRIT) flow diagram is provided in Fig. 1, and a populated SPIRIT checklist is provided in Additional file 1.

**Fig. 1 Fig1:**
[figure not shown]
Standard Protocol Items: Recommendations for Interventional Trials (SPIRIT) figure for patient participations. ODI Oswestry Index Disability, NPRS Numeric Pain Rating Scale, EMG electromyographic, FABQ Fear-Avoidance Beliefs Questionnaire

**Table 1 Tab1:** Items included in the Template for Intervention Description and Replication (TIDieR) checklist: information to include when describing an intervention. Full version of checklist provides space for authors and reviewers to give location of the information

Item no.	Item
Brief name	
1	OVM
Why	
2	Visceral osteopathy is described as a manual treatment performed directly on the viscera with the goal to normalize the mobility dysfunction of the organ and try to eliminate fascial restrictions and relax the visceral spasms.
What	
3	As previously described, the treatment with OVM is manual therapy, because of this it is performed only with the hands.
4	Manual techniques will be performed in the small and large intestine of the volunteers. At the beginning of each session, individuals will be assessed and points of spasms of the visceral musculature of the small and large intestine or fascial restriction will be located. All the techniques are described in the visceral osteopathy book [31].
Who provided	
5	The physiotherapist who will perform the treatment is graduated in physiotherapy for 13 years and she has > 10 years of experience in this type of treatment. She is an osteopath certified by Madrid’s Osteopathy School (Escuela de Osteopatía de Madrid).
How	
6	Six individual weekly sessions of 15 min each will be carried out.
Where	
7	The sessions will be carried out in a private clinic in the city of Rondonópolis/MT.
When and how long	
8	The participants will receive six individual weekly sessions. The duration will be 15 min for each session.
Tailoring	
9	At the beginning of each session, the volunteers will be evaluated according to visceral spasms in the large and small intestine and fascial restriction for manual treatment according to the need of each patient. After the evaluation, the patients will be treated with techniques of visceral osteopathy in the large and small intestine to normalize the visceral musculature spasms.
Modifications	
10^a^	–
How well	
11	Osteopaths are trained to identify visceral spams and/or fascial restriction when they do osteopathy’s formation. We try to propose a treatment respecting the individuality of the patients and seeking to reproduce better the clinical practice. As previously proposed by Panagoupols et al. [11] and Tamer et al. [16]).
12^a^	–

^a^If a checklist is completed for a protocol, these items are not relevant to protocol and cannot be described until the study is complete

### Sample size calculation

The sample size was calculated using G Power 3.1.9.2 software. This calculation was based on the detection of a 10-point difference on the ODI and 2.5-point difference on the NPRS, which have been identified as the minimum clinically important differences [33]. A sample size of 32 participants per group would provide a 90% power to detect a clinically important difference between groups, assuming a common standard deviation of 12 on the ODI [34] and 3.0 on the NPRS and a two-sided hypothesis with an alpha level of 0.5. The sample will be increased by 20% to compensate for possible dropouts, leading to 38 individuals in each group (overall sample = 76 participants).

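### The 90% power belongs to one unadjusted two-sample t-test, while the plan decides by repeated-measures ANOVA with Bonferroni post hoc tests; for a raw-score contrast with 32 per group it is an upper bound

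*Protocol article*

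**What the plan says.** **Sample size calculation.** The software is named ("The sample size was calculated using G Power 3.1.9.2 software") but the test is not. The target is "detection of a 10-point difference on the ODI and 2.5-point difference on the NPRS", "assuming a common standard deviation of 12 on the ODI" and "3.0 on the NPRS and a two-sided hypothesis with an alpha level of 0.5". The conclusion is "A sample size of 32 participants per group would provide a 90% power to detect a clinically important difference between groups", after which the groups are enlarged to 38 each (76 in total) for dropout. No multiplicity allowance, number of repeated measurements or within-patient correlation is given.

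**Outcome measures.** Pain intensity (NPRS) and disability (ODI) are both primary, and both are assessed "after the six weeks of treatment and three months after randomization, because pain is the most common reason". Each primary outcome therefore has two primary time points.

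**Statistical analysis.** The independent t-test is kept for anthropometric differences between groups. For outcomes, "Repeated-measures analysis of variance (ANOVA) followed by the Bonferroni post hoc test will be used to determine the effects of treatment", with two groups and four evaluations: before treatment, after one session, after six weeks and three months after randomization. The section also specifies intention-to-treat with last observation carried forward, and a 0.05 significance threshold. It does not say which comparisons the Bonferroni step covers.

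**The concern.** A power statement is informative only for the test that will decide the question. Here the stated power appears to describe a single, uncorrected two-group comparison at one visit, while the stated analysis reaches a visit-specific group difference through a repeated-measures model and a Bonferroni post hoc step. If that step corrects across visits, each group contrast is tested at less than 0.05, and the sample size calculation makes no allowance for this.

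What is at stake is how a non-significant result is read. Set against a claimed 90% power, it would look like fairly strong evidence against a 10-point ODI or 2.5-point NPRS difference. If the contrast was in fact tested at 0.025 or 0.0125, the chance of missing such a difference would be larger than the 10% the protocol implies.

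**Working it through.** **Inputs from the sample size section.** ODI difference 10, SD 12; NPRS difference 2.5, SD 3.0; two-sided; power 90%; 32 per group, enlarged to 38. Alpha is printed there as 0.5, whereas the statistical analysis section uses 0.05.

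**Standardised difference.** 10/12 = 2.5/3.0 = 0.833, so one calculation serves both primary outcomes.

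**Formula.** Two-sample t-test with n per group: df = 2n − 2, noncentrality = 0.833 × √(n/2), power from the noncentral t distribution at two-sided level 0.05/m, where m is the number of contrasts in the Bonferroni family.

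**Reproducing the stated figure (m = 1).** With n = 32, df = 62, noncentrality = 0.833 × √16 = 3.33 and the critical value is 2.00. Power is 90.7%. With n = 31 it is 89.8%, so 32 is the smallest group size that reaches 90%. The other versions tried do not lead to 32: one-sided 0.05 gives 95.1% at n = 32, and alpha 0.5 as printed gives 99.6% and would need only 11 to 12 per group. The printed 0.5 looks like a slip for 0.05 and is a separate matter.

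**Same contrast under a Bonferroni correction across visits**

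| Contrasts corrected for (m) | Level per contrast | Power, 32 per group | Power, 38 per group |
|---|---|---|---|
| 1 (no correction across visits) | 0.05 | 90.7% | 94.8% |
| 2 (six weeks and three months) | 0.025 | 84.7% | 90.8% |
| 3 | 0.0167 | 80.6% | 87.9% |
| 4 (all evaluations) | 0.0125 | 77.4% | 85.5% |
| 28 (all pairs of the 8 group-by-evaluation cells) | 0.0018 | 53.1% | 65.1% |

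The 38-per-group column assumes that everyone randomized enters the analysis through last observation carried forward, and that carried values neither dilute the effect nor change the SD.

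**The omnibus test.** With 32 per group, the group-by-evaluation F test at 0.05 has about 79% to over 99% power for assumed correlations of 0.3 to 0.7, depending on the assumed mean profile (compound symmetry, full effect at six weeks and three months, various effects after one session). By itself it does not show a difference at a primary time point. In simulation, requiring both a significant F test and a significant raw-score contrast at a primary time point gives about 74% to 91% over the same correlations, even with no Bonferroni correction.

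**Sensitivity to the form of the contrast (32 per group, m = 4).** Baseline-adjusted: 89.5% at an assumed correlation of 0.5 and 98.0% at 0.7. Change score: 59.8%, 77.4% and 95.5% at 0.3, 0.5 and 0.7. The protocol gives no correlation and names no baseline covariate for the outcome analysis.

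**The case against.** The strongest reply is that the Bonferroni family is undefined. With two groups there is only one pair to compare at each visit. If the correction runs only within a visit, nothing is lost and power stays at 90.7%. That stands. A reader might infer from the plan that the true power is 77% to 85%, but the protocol does not fix the family of two to four on which that range depends.

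Three further points have force:

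- Intention-to-treat with carried-forward values could bring 38 per group into the analysis. With a family of two, power is then 90.8% and the stated 90% survives, provided carrying forward does not dilute the effect.
- A baseline-adjusted analysis could recover the loss or more, and the interaction F test can itself exceed 90%. A change-score contrast at low correlation would go the other way.
- A family of four is less natural than two for the primary outcomes. Only two visits are primary, and the NPRS is asked as current pain for the immediate effect but as a seven-day average for the later visits.

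It can also be said that sizing a repeated-measures trial by a simple two-group comparison is common, and that an analysis plan not shown may define the family. That would explain how the gap arose, but the article itself states a power figure and an analysis that do not correspond. Nor is the calculation wrong in itself: 32 per group is right for the test that was powered.

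**Conclusion.** The point holds as a mismatch between the powered test and the planned test. For a raw-score group contrast at one primary time point with 32 per group, 90.7% is the most the design can offer. It applies only if contrasts are not corrected across visits and a significant interaction is not required first. Correcting over the two primary time points gives 84.7%, which raises the type II error from 9.3% to 15.3%. Correcting over four evaluations gives 77.4%, a type II error of 22.6%. With 38 per group and no dilution, the powers are 90.8% and 85.5%.

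These figures rest on the protocol's own differences and SDs, on alpha 0.05 rather than the printed 0.5, and on assumed families of two and four. They are conditional illustrations. The protocol does not support a firm statement that the trial has 77% to 85% power or is underpowered, because the family and the correlation are both unstated. What can be said is that the 90% cannot be attached to the planned analysis as it is written.

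**What to change.** Two wording changes:

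1. **Statistical analysis:** state that, for each primary outcome, the Bonferroni family is the two contrasts of manipulation against sham at six weeks and at three months after randomization, each tested at two-sided 0.025.
2. **Sample size calculation:** name the test, and restate power as about 85% per contrast with 32 evaluable per group for a 10-point ODI difference (SD 12) or a 2.5-point NPRS difference (SD 3.0). Add that it is about 91% if all 38 per group are analysed and carried-forward values do not weaken the effect.

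The cost is a less favourable stated power at 32 per group. No extra patients are needed, and both primary time points stay primary. Keeping 90% by making six weeks the only primary time point is not recommended, because it would demote a time point that the outcome section makes primary.
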